### Intervention

The rehabilitation intervention will be administered at the rehabilitation medical center of the Seventh People’s Hospital of Shanghai University of Traditional Chinese Medicine. All participants will receive the CRP recommended by the neuro-rehabilitation guidelines [28, 29], which will include stretching, passive and active limb movements, proprioceptive neuromuscular facilitation, muscle strengthening, and different reaching, grasping and manipulating actions that are motivational and appropriate for the participants. Based on the CRP (20 min), Group A will receive FES (20 min); Group B will receive RAT (20 min); and Group C will receive FES-RAT (20 min). The intervention for the three groups will be provided for 60 sessions (5 sessions per week, 12 weeks), each lasting 40 min.

### Functional electrical stimulation (FES)

A synergy-based multi-channel FES device was developed using the Fourier ElectroFortis Programmable Stimulator, which can stimulate multiple muscles with customized parameters. An experimenter computer GUI application was created to configure the following basic stimulation parameters: the frequency, minimum and maximum intensity, pulse duration, ramp time, synchronization and order of stimulations, type of user interactions and number of repetitions [30]. The stimulation envelope will be specified as the concatenated piecewise linear functions (e.g., rising phase, plateau phase and falling phase), and will be allowed to be preloaded to the FES device [11]. Synergy-based FES will be applied to stroke participants and constructed from the muscle synergies of healthy controls. The raw EMG signals of the dominant upper limb muscle will be obtained from healthy controls performing the RTG task [31]. After processing with a filter and rectification, the muscle synergy pattern will be extracted by non-negative matrix factorization (NMF) in the previous study [32]. Then, the muscle synergy pattern will be converted into the FES stimulus envelope according to the conversion formula proposed by Niu [11].

The training objective for FES therapy emphasizes functional arm reaching, hand opening and grasping. During RTG training, gross motor tasks (proximal muscles) are started in the early stages of therapy, followed by fine movement control tasks (distal muscles) [30]. As participants improve, stimulation will gradually be reduced to a minimum and eventually phased out. Before the intervention, all operators will receive the homogenization training of the FES treatment scheme. The specific steps are as follows:Identify the functions to be trained and select the order of the tasks to be retrained.Identify the stimulated muscle and apply self-adhesive electrodes over the identified motor muscles: including the biceps brachii, triceps brachii lateral head, triceps brachii long head, anterior deltoid, posterior deltoid, pectoralis major, and brachioradialis [33] (Fig. 2).Identify and record the different stimulation thresholds: • the motor threshold: when a palpable or a visible contraction is produced; • the sensory threshold: when the participants feel the current for the first time; and • the maximum threshold: beyond which the patient does not tolerate an increase in current amplitude.Preloaded the muscle synergy pattern of the healthy controls to the FES device.Explain what to expect when FES is started and instruct the participants to make an active attempt to perform the intended movement.Repeat the stimulus protocol and ensure an adequate rest time.Turn off the stimulator when the treatment is completed, remove the electrodes and inspect the skin underneath for any redness.

**Fig. 2 Fig2:**
[figure not shown]
The points of the identified motor muscles in FES

### Robotic-assisted therapy (RAT)

The Fourier intelligence upper-limb robotic system (Fourier, Shanghai, China), which is an intelligent rehabilitation training system designed especially for stroke patients with upper limb or motor dysfunction, will be used for robotic-assisted therapy in this study. The system can provide passive, assistive, and active planar movements around the shoulder, elbow, and wrist joints [31]. More importantly, the system is able to establish the movement trajectory of the manipulator according to the upper limb movement pattern during ADLs or target tasks, which can be customized for specific tasks. The largest body of clinical evidence has been amassed for this robotic system; the system has been successfully tested on over 500 stroke patients in clinical studies, and there are approximately 100 robots in use worldwide [34].

During treatment, participants will perform the RTG task displayed in a game scene that generates real-time auditory and visual feedback [35] (Fig. 3). Each participant will be required to sit on a chair, and his or her affected UE will be strapped to the robot arm. Machine settings such as the height of the platform, the length of the robot arm, and the amount of assistance force will be adjusted according to each participant’s personal characteristics. The treatment content (game tasks/motor or task-oriented training) settings and doses will be the same for all participants in the middle activity range. RAT will provide repetitive and high-intensity training in a cost-effective manner. When participants perform the RTG movement, the objects will be exhibited on the computer screen using a virtual hand, allowing them to receive timely feedback on their performance from the robotic device. The robot’s UE movement patterns are functional and the joints are isolated, which minimizes synergic movement in stroke patients.

**Fig. 3 Fig3:**
[figure not shown]
RAT tasks for upper limb

### FES-RAT

For FES-RAT treatment, the participants will receive FES when performing the RAT task (Fig. 4). The frequency, repeated time and rest time will be consistent with separate FES or RAT. To realize the synchronous triggering and control of FES and RAT, the control terminal will be developed through a multifunctional I/O Device (NI6255, National Instruments Inc., Austin, TX) [36]. The FES stimulus envelope and manipulator kinematic datasets will be aligned via the start switch trigger recorded digitally in HANDoVR, and the analog reading of the digital output will be sent from HANDoVR to MATLAB.

**Fig. 4 Fig4:**
[figure not shown]
FES combined RAT in upper limb training

### To reduce the dropout rate

To improve treatment adherence and reduce the likelihood of participants dropping out of the study, the therapists will contact the participants by texting, voice and video through an intelligent follow-up system, which is a small program embedded in WeChat app. The therapists will also regularly phone the participants if they have difficult in receiving information on smartphones. Through above strategies, the research team can confirm their appointments, discuss the subsequent intervention step as well as avoiding any barriers to adherence.

### Outcome measurements

All outcome measurements will be assessed by a professional rehabilitation assessor who will be blinded at baseline (T1), 6 weeks (T2) and 12 weeks (T3) during the intervention and at 3 months (T4) and 6 months (T5) during the follow-up period. Data on the demographic and clinical characteristics of the participants will be collected at T1.

### Primary outcome measurements

#### Upper extremity function

The primary outcome is upper extremity function evaluated by the upper extremity section of the Fugl-Meyer scale. The FMA-UE has outstanding intrarater (ICC = 0.997) and interrater (ICC = 0.993) reliability for assessing proximal-to-distal and synergistic-to-isolated movement behavior in stroke patients [37, 38]. The highest possible total score is 66, with 33 items and ordinal scoring from 0 to 2, with a higher score indicating more effective function. Additionally, both the proximal (range 0–42) and distal (range 0–24) subscores of the FMA-UE will also be considered.

#### Biomechanical assessment of reach-to-grasp movements

The RTG movements of the affected upper extremity will be assessed by three-dimensional biomechanical analysis. The RTG performance test will be selected because prior research has demonstrated that concentrating purely on task outcome measures fails to differentiate between neural recovery processes and the development of efficient but abnormal compensatory movement patterns [39–42]. Multiple authors have utilized the kinematic analysis of three-dimensional RTG movements as a viable means to analyze the motor control process and identify the normalization of motor function in persons with stroke [40, 42, 43]. The biomechanical evaluation protocol will be based on a previously established, standardized kinematic analysis testing protocol for RTG movements (i.e., drinking) [40, 42]. More comprehensively, the present study protocol will further complement the evaluation of muscle activation and synergy patterns.

The standardization of the RTG task will be divided into five phases: (1) reaching to grasp a glass, (2) forward transport of the glass to the mouth, (3) drinking a sip of water, (4) transporting the glass back to the table, and (5) returning the hand to the initial position [41]. The details of the test task are as follows: the participants will sit comfortably at a table, with 90° knee and hip flexion and 90° elbow flexion with the upper arm vertical and forearm horizontal. The grasping target will be rigidly mounted on the testing table in front of the subject, aligned with the participant’s affected shoulder and at a distance of 35 cm. Data from each participant will be collected from 5 successful trials, and the rest time between each trial will be approximately 30 s.

Before the biomechanical test, the reflected markers and EMG sensors will be placed on the anatomical landmarks and targeted muscle respectively. Eight markers will be affixed on the tested hand (III metacarpophalangeal joint), the wrist (styloid process of the ulna), the elbow (lateral epicondyle), on both shoulders (acromion), the trunk (sternum), the forehead and the drinking glass. EMG sensors will be placed on the following ten muscles of each participant’s shoulder, arm and hand on the affected side: the first dorsal interosseous (FDI), flexor digitorum superficialis (FDS), extensor digitorum communis (EDC), extensor indicis (EI), abductor pollicis brevis (APB), extensor pollicis brevis (EPB), biceps brachii (BB), triceps brachii (TB), anterior deltoid (AD), and posterior deltoid (PD). A 10–camera infrared motion capture system (sampling rate: 100 Hz; Vicon Motion Systems, Oxford, United Kingdom) and a Delsys EMG system (sampling rate: 1000 Hz; Delsys Inc., Natick, MA) will acquire three-dimensional kinematics and muscle activation information, respectively.

The outcomes of kinematic analysis will include the following: the movement time (ms), peak velocity (cm/s), time to peak transport velocity (ms), trajectory length ratio (%), trajectory smoothness, peak aperture (cm), peak aperture velocity (cm/s), opening distance (cm) and reach grasp coupling index. The definitions of kinematic variables have been described in several previous studies [36, 40, 42–44]. Additionally, the muscle synergy pattern will be extracted from the raw EMG signals through the method of non-negative matrix [11, 32], which considers muscle activation as the linear combination of multiple muscle components (muscle vectors) with the corresponding activation coefficients (time profiles).

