**Methods:**

This will be an assessor-blinded randomized controlled trial involving a 12-week intervention and a 6-month follow-up. Stratified randomization will be used to equally and randomly assign 162 stroke patients into the FES + conventional rehabilitation program (CRP) group, RAT + CRP group and FES-RAT + CRP group. Interventions will be provided in 5 sessions per week, with a total of 60 sessions. The primary outcome measurements will include the Fugl-Meyer Assessment and Biomechanical Assessment of RTG movements. The secondary outcome measurements will include quality of life and brain neuroplasticity assessments by MRI. Evaluations will be performed at five time points, including at baseline, 6 weeks and 12 weeks from the start of treatment, and 3 months and 6 months following the end of treatment. A two-way analysis of variance with repeated measures will be applied to examine the main effects of the group, the time factor and group-time interaction effects.

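### The eight-marker set has no marker on a digit, so two to four of the nine kinematic variables cannot be derived as written, and the fixed grasping target contradicts the drinking task

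*Protocol article*

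**What the plan says.** The abstract of the protocol article gives the test primary status: "The primary outcome measurements will include the Fugl-Meyer Assessment and Biomechanical Assessment of RTG movements". The test also stands under the heading for primary outcome measurements.

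The section on biomechanical assessment of reach-to-grasp movements then specifies four things.

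- **Markers.** "Eight markers will be affixed on the tested hand (III metacarpophalangeal joint), the wrist (styloid process of the ulna), the elbow (lateral epicondyle"), and after that "on both shoulders (acromion), the trunk (sternum), the forehead and the drinking glass". The kinematics are recorded with a ten-camera infrared system.
- **Variables.** Five concern the movement of the arm: "the movement time (ms), peak velocity (cm/s), time to peak transport velocity (ms), trajectory length ratio (%), trajectory smoothness". Four concern the grasp or its timing against the reach: "peak aperture (cm), peak aperture velocity (cm/s), opening distance (cm) and reach grasp coupling index".
- **Definitions.** These are left to references: "The definitions of kinematic variables have been described in several previous studies".
- **Task.** There are five phases of drinking from a glass, the second being "2) forward transport of the glass to the mouth", followed by a sip, the return of the glass and the return of the hand. On the set-up the section says: "The grasping target will be rigidly mounted on the testing table in front of the subject", at a distance of 35 cm.

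**The concern.** Two parts of the specification do not fit together.

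First, grip aperture is the distance between opposing digits. It needs at least two tracked points on the digits, and the marker list appears to offer none. If so, the hand-opening part of the test would give no data at any of the five assessments, and what is left would describe the reach but not the opening of the hand. Aperture that was not recorded at baseline cannot be reconstructed later, and recruitment opened on 1 May 2023.

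Second, a glass that is fixed to the table cannot be lifted to the mouth. As it stands, the text does not give an assessor one set-up to reproduce at every visit.

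**Working it through.** No sample-size or power arithmetic bears on this point. The check is a count, followed by a comparison of sentences.

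**Step 1: is the marker list complete?** The article states eight. Counting the sites it names:

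| Site | Markers |
|---|---|
| Hand (third metacarpophalangeal joint) | 1 |
| Wrist | 1 |
| Elbow | 1 |
| Shoulders, both | 2 |
| Trunk | 1 |
| Forehead | 1 |
| Glass | 1 |
| **Total** | **8** |

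1 + 1 + 1 + 2 + 1 + 1 + 1 = 8, which reproduces the stated figure. The list is closed, so no marker is left over for the digits. Digit points available: 0. Digit points needed for an aperture: at least 2.

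**Step 2: is there another source of finger position?** None is named for this test. The EMG sensors on hand muscles record activation, not position. The HANDoVR component in the FES-RAT section belongs to the synchronisation of treatment, not to outcome assessment.

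**Step 3: which variables depend on the digits?**

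| Variable | Obtainable from the listed markers? |
|---|---|
| Movement time, peak velocity, time to peak transport velocity, trajectory length ratio, trajectory smoothness (5) | Yes, from the hand or wrist marker |
| Peak aperture | No |
| Peak aperture velocity | No |
| Opening distance | No, on the plain meaning of the term; not defined in the article |
| Reach grasp coupling index | Probably not; not defined in the article, and its dependence on aperture is inferred from its name |

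**Step 4: range.** 5 + 4 = 9 variables in all.

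- Peak aperture and its velocity only: 2/9 = 22%.
- With opening distance: 3/9 = 33%.
- With the coupling index as well: 4/9 = 44%.

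**Step 5: the task.** Phases 2 to 4 have the glass carried to the mouth, drunk from and carried back. The marker list puts a marker on the drinking glass. The phase list names no object to be grasped other than the glass. One sentence says that the grasping target is fixed to the table. Read together, that sentence conflicts with the phase list, and a marker on a glass is most naturally a marker on something that moves.

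**The case against.** The strongest reply is that this is a condensed article which sends the reader to earlier studies for the kinematic definitions. Those studies might define opening distance or the coupling index without digit positions. That stands for the coupling index and in part for opening distance, which is why the size is given as a range. A reader might infer that all four variables are certainly unmeasurable, and the article does not support that. The reply does not rescue peak aperture or its velocity: a cited definition cannot recover a distance between digits from a single knuckle marker. Condensation does not explain the gap either, because the stated number and the named sites agree exactly.

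A second reply is that little hangs on this. The upper extremity function section calls the FMA-UE the primary outcome, and the sample size rests on it. It is fair that the FMA-UE comparison, the five arm-movement variables and the EMG synergy patterns are untouched by the marker gap. The abstract and the section heading nevertheless list the biomechanical test as primary, so the gap lies within a declared primary outcome.

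On the task, a reader might infer that the test cannot be performed, or that two different tasks are being run and the remaining variables depend on which. The documents do not show that. Everything except one sentence describes a movable glass, and only one task is named. The sentence may have been meant to convey a standard starting position. What is established is a contradiction in the text.

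Finally, a reader might infer that data have already been lost. The article does not show which markers the laboratory has used, so any statement about loss holds only if the test is conducted as written.

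**Conclusion.** The point holds as two inconsistencies within one section.

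1. If the test is conducted as written, peak aperture and peak aperture velocity cannot be derived, and neither can opening distance on its plain meaning. The coupling index is probably affected. The size is 2 to 4 of 9 kinematic variables, depending on definitions that the article does not give. The assumptions are that aperture means a distance between digits and that no finger-tracking device outside the article is in use.
2. The fixed grasping target contradicts the drinking phases and the marker on the glass. This assumes that the target is the glass, which is the natural reading because the first phase is a reach to grasp a glass.

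The first needs correction before more baselines are recorded, because a missing baseline cannot be recovered. The second is a correction of wording unless the laboratory has in fact used a fixed object.

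**What to change.** 1. **Establish the facts first.** Find out which markers and which glass set-up have been used since recruitment began. If digit markers and a free-standing glass were already in use, correcting the text is enough.
2. **If no digit markers were used,** take one of two routes:
   - Add one marker on the thumb tip and one on the index fingertip (8 + 2 = 10), and restrict the aperture-based analyses to participants whose baseline was recorded with them. Because allocation is revealed only after all baseline assessments, this restriction rests on a feature fixed before assignment and keeps the comparison randomised, in a smaller sample.
   - Remove the affected variables by a dated amendment made without reference to outcome data.
3. **State the definitions** of opening distance and the coupling index, so that it is clear whether they depend on the digits.
4. **Reconcile the task text.** Replace the fixed target with a free-standing glass at a marked start position 35 cm away, consistent with the five-phase drinking task, and use that set-up throughout. Cutting the later phases instead would contradict the drinking protocol the article adopts, and could change the test after recruitment began.

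The cost is two extra reflective markers per session on the existing cameras, and a protocol correction. Participants already recorded without digit markers would lack these variables.

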### Secondary outcome measurements

#### Quality of life

The QOL of the participants will be measured by the Stroke-Specific Quality of Life Scale (SS-QOL). The SS-QOL was created in 1999 to quantify the impacts of stroke and assessed the efficacy of treatment strategies with high reliability (0.98) [39, 40]. The SS-QOL is a long 49-item stroke-specific instrument that provides a total QOL score and 12 subscale scores associated with mobility, cognition, mood, functionality, and social roles, with higher scores indicating a better QOL.

#### Brain neuroplasticity

Magnetic resonance imaging (MRI) will be used to investigate the brain mechanisms of rehabilitation, particularly in regions related to motor learning and motor control. MRI data will be acquired using a 3.0 T magnetic resonance scanner (Siemens Magnetom Verio Syngo MR B17, Germany) with a 32-channel phase-array head coil at the Department of Medical Imaging of the Seventh People's Hospital of Shanghai University of Traditional Chinese Medicine. The following three MRI modalities will be acquired [41–43]: (1) high-resolution anatomical MRI (T1-MRI) for estimating the anatomical parameters of the cortex, the subcortex, and structural connectivity; (2) resting-state functional MRI (RS-fMRI) for estimating the functional connectivity of brain regions; and (3) diffusion tensor imaging (DTI) for estimating the tract-graphic parameters of white matter and the microstructure of gray matter.

### Data management and monitoring

The project and data management, data analysis and data monitoring will be supervised by the independent Data Monitoring Committee (DMC) affiliated with the Scientific Research Innovation Platform of the Seventh People's Hospital of Shanghai University of Traditional Chinese Medicine. The dataset will be stored, analyzed and archived in a pseudonymized manner to entirely protect individual privacy and minimize bias.

### Statistical analysis

All statistical analyses will be performed with IBM SPSS (IBM Corp. Released 2013. IBM SPSS Statistics for Windows, Version 22.0. Armonk, NY: IBM Corp.) by statisticians who are blinded to the group allocation. The analyses will be performed on an intention-to-treat basis. The Shapiro–Wilk (SW) test will be used to examine the normal distribution of the continuous variables comprising demographic and outcome measures. Continuous variables will be described as the mean ± SD for those with normal distributions or the median for those with nonnormal distributions, and categorical variables will be described as the frequency. The χ^2^ test or Fisher’s exact test will be used to examine the comparisons among the three groups for categorical variables. When the normality of data distribution is determined, two-way of variance with repeated measures will be applied to examine the main effects of the group and time factors, as well as the group-time interaction effects. A simple effect post hoc analysis will be conducted when the time-group interaction is significant. Furthermore, the linear mixed model will be adjusted for age, sex and type of stroke if homogeneity is not found. The significance level for all statistical tests will be set at 0.05, corrected for multiple comparisons using the Bonferroni-adjusted method and accompanied by a 95% confidence interval.

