### Sample size calculation

The G*power software was utilized to determine the minimum sample size required to detect a significant between-group difference in the present research [24]. In a study of RAT for upper-extremity poststroke rehabilitation, Takebayashi et al. [25] used the minimal clinically significant difference as a reference (4.25 points), the mean difference in the FMA-UE score between patients in the RAT and CRP was 4.50 points and standard deviations between patients were 6. Based on a prior two-way repeated analysis of variance (ANOVA) F test, with a power of 0.80, an effect size of 0.158, three groups, five measurements, correlation among repeated measures of 0.5, and an alpha level of 0.05, 129 participants were required for this study. To account for a conservative drop-out rate of 20%, the final sample size will therefore be 54 participants in each group, for a total of 162 participants.

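### Intention-to-treat does not fit repeated-measures ANOVA in SPSS unless missing visits are imputed, and tests on the trial's own data condition the choice of model

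*Protocol article*

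**What the plan says.** All of the following is in the protocol article.

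- **Population** (Statistical analysis): "The analyses will be performed on an intention-to-treat basis".
- **Software** (same section): "All statistical analyses will be performed with IBM SPSS", version 22.
- **Main method** (same section): "When the normality of data distribution is determined, two-way of variance with repeated measures will be applied", to test group, time and their interaction. The abstract names the same method without any condition and mentions no mixed model: "A two-way analysis of variance with repeated measures will be applied to examine the main effects of the group". The Sample size calculation is also built on a two-way repeated-measures ANOVA with three groups and five measurements.
- **Normality check** (Statistical analysis): the Shapiro–Wilk "test will be used to examine the normal distribution of the continuous variables comprising demographic and outcome measures".
- **Mixed model** (same section): "Furthermore, the linear mixed model will be adjusted for age, sex and type of stroke if homogeneity is not found". The article does not say whether homogeneity refers to variances or to baseline characteristics.
- **Visits** (Outcome measurements): baseline (T1), 6 weeks (T2), 12 weeks (T3), then 3 and 6 months into follow-up (T4, T5).
- **Drop-out** (Sample size calculation): "To account for a conservative drop-out rate of 20" per cent, the total becomes 162, or 54 per group.

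The article states no rule for a missing visit.

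**The concern.** The SPSS repeated-measures procedure works on one complete row per participant. Someone seen at baseline, 6 weeks and 12 weeks who misses only the last follow-up visit is removed from the whole model, and so from the week-12 comparison as well. A plan that expects one participant in five to drop out, promises intention-to-treat and relies on this procedure holds two commitments that do not fit together, and nothing in the article reconciles them.

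Two things are at stake. Outcome data already collected would go unused. The comparison of completers could also be biased if the reasons for leaving relate to recovery and differ between arms. Participants cannot be blinded (Discussion, limitations), so arm-related drop-out is conceivable, although the article gives no evidence of it.

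The second strand is that the method is not fixed before the data are seen. The ANOVA depends on a test of the outcome values. The mixed model, or its adjustment, depends on a check that is not defined. FMA-UE is a bounded 0–66 sum of ordinal items, and nine kinematic variables are listed, so different outcomes may well take different routes.

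**Working it through.** **Inputs from the article:** 129 participants required before drop-out; 20% drop-out; 162 randomised, 54 per arm; five visits; SD 6 FMA-UE points; correlation 0.5; reference difference 4.25 points. The figure of 129 is taken as given here.

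**1. The plan's own figure.** 129 / (1 − 0.20) = 161.25, rounded up to 162 = 3 × 54. The drop-out step reproduces. It also shows that the design expects about 129 participants with complete data.

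**2. Complete rows at the planned drop-out.** About 129 of 162 remain (80%), and 162 − 129 = 33 randomised participants are left out of every comparison.

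**3. Adding missed visits among those who stay (assumption).** Baseline is complete, because envelopes are opened only after the baseline assessments. A complete row therefore needs T2 to T5, and with independent misses at rate *p* the number is 129 × (1 − *p*)⁴.

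| *p* per visit | Complete rows with 20% drop-out | Complete rows with no drop-out, 162 × (1 − *p*)⁴ |
|---|---|---|
| 2% | 129 × 0.922 = 119 | 149 |
| 5% | 129 × 0.815 = 105 | 132 |
| 10% | 129 × 0.656 = 85 | 106 |

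**4. Observed scores that are discarded.** The article does not say when drop-out happens. Assume it is steady, reaching 5%, 10%, 15% and 20% at T2 to T5.

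- Possible post-baseline scores: 162 × 4 = 648.
- Observed: 162 × (0.95 + 0.90 + 0.85 + 0.80) = 162 × 3.5 = 567 (87.5%).
- Used with complete rows only: 162 × 0.80 × 4 = 518 (80%).
- Discarded although observed: 567 − 518 = 49.
- At week 12 alone: 162 × 0.90 = 146 observed, against 162 × 0.80 = 130 used, so about 16 participants have a week-12 score that is not analysed.

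**5. Possible bias (illustration).** A simulation used two arms of 54, SD 6, correlation 0.5, no true difference, and about 20% drop-out related to the last observed score in opposite directions in the two arms. The drop-out pattern is an assumption. The completers' difference at T5 was off by 1.0 point (simulation standard error 0.07), and the likelihood-based estimate from all observed visits by −0.06. Against the article's 4.25-point reference, 1.0 / 4.25 = 24%.

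**6. The conditions set side by side.**

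- Normality shown: ANOVA, hence complete rows unless missing visits are imputed.
- Normality not shown: the article gives only the median as a description and names no inferential method.
- Homogeneity not found: on one reading a mixed model replaces the ANOVA and uses all observed visits. On another, only the adjustment for age, sex and type of stroke is switched on.

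On either reading, something in the main analysis depends on a check of the trial's own data.

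**The case against.** The strongest reply is that complete-case analysis is inferred. The article says intention-to-treat and never says that incomplete participants are dropped. If a full plan imputes missing visits before the ANOVA, nobody is lost, and a short article may leave imputation to that plan. This stands, and it is why the point is conditional. It does not remove the dependence on pre-tests.

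Second, the homogeneity sentence may govern only covariate adjustment. The covariates it lists are baseline characteristics, which favours that reading. This also stands. The abstract and the sample size calculation nevertheless point to the ANOVA as the main analysis.

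Third, the reduced number is planned for: the inflation from 129 to 162 pays for it, the 20% is described as conservative, and retention measures are set out. A reader might infer an unplanned shortfall in numbers; the documents do not support that. What remains is the waste of observed scores and the possible bias.

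Fourth, no passage says that drop-out depends on outcome or arm, and all arms receive an active device treatment in sessions of the same length. The 1.0-point figure shows what can happen under one assumed pattern and predicts nothing for this trial.

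Last, the missing method for non-normal outcomes is a detail that an article may leave to the analysis plan. It is not counted as a fault here.

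**Conclusion.** The concern holds in conditional form. The stated population and the stated main method conflict once a visit is missing, unless values are imputed, and the article does not say that they are. Without imputation about 129 of 162 (80%) would be analysed at the planned drop-out, and fewer if those who stay miss single visits: 105 at 5% per visit and 85 at 10%, both assumed rates. Under steady drop-out, also assumed, about 49 observed post-baseline scores would go unused. Bias requires drop-out that is related to outcome and differs by arm, for which the documents offer no evidence either way.

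The conditioning of the analysis on tests of the trial data is explicit for the ANOVA. For the mixed model it is explicit at least as regards adjustment.

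Three stronger readings go beyond the text. A reader might infer that the pre-tests choose the analysis population; no section says so, and it would only follow in effect if the ANOVA route uses complete rows and the mixed-model route all observed data. A reader might infer that all 33 or so dropouts would forfeit 6- and 12-week scores; those who leave before week 6 have none to forfeit. And a reader might take complete-case analysis as declared, which it is not.

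**What to change.** In the Statistical analysis section, make the linear mixed model already named there the single, unconditional main analysis for every repeated continuous outcome:

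- visit as a categorical factor, with group, visit and group-by-visit terms;
- covariates fixed in advance, including the stratification factors (sex, stroke type, dominant hand);
- all observed data, with baseline in the outcome vector, so that every randomised participant is included in the allocated arm. A rule requiring at least one post-baseline value would be narrower than all randomised and should be avoided.

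Keep Shapiro–Wilk and any homogeneity check as diagnostics that do not change the main model. The mixed model relies on data being missing at random, so add a sensitivity analysis for departures from that. Bring the abstract's analysis sentence into line.

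The cost is one reworded paragraph, one sentence in the abstract and slightly more analysis work; the model is available in the same software. The main analysis would no longer match the ANOVA behind the sample size, which should be acknowledged in the Sample size calculation. The change should be made before any analysis by arm.
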